#### Treatment—day 0 until emergence from PTA (or 6 months maximum)

The treatment period will last from day of completion of baseline assessments until the patient is deemed to have emerged from PTA or until 6 months have elapsed. Emergence from PTA is defined as the first of three consecutive days on which a score of 12/12 on the WPTAS is achieved. Participants will be administered their randomised dose. They will also receive optimal environmental management as per guidelines [7]. WPTAS and ABS scores will be recorded by nursing staff or the patient’s clinical neuropsychologist. Need for dosage escalation and rescue medication use will be monitored by study staff. To describe concomitant care and inform health-economic evaluation, the number of patients on the ward, therapy hours and number of sessions and medication use including name and dose regimen will be recorded from the participant’s medical file.

AE monitoring will occur weekly. Clinically significant changes in these parameters will be recorded as AEs and a decision made by the treating doctor in consultation with a psychiatrist and the DSMC as to whether serious AEs necessitate withdrawal from the study.

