#### Secondary outcomes

To examine the safety of olanzapine administration in PTA patients: Difference between olanzapine and placebo groups’ mean number of AEs (as captured via trial bloodwork, Adverse Events Questionnaire, Simpson-Angus Scale, measures of weight, BP, HR, WC) during PTA.To determine whether olanzapine treatment reduces the number of clinically agitated days during PTA: Difference between olanzapine and placebo groups’ mean number of clinically agitated days (ABS score > 21) during PTA.To determine whether olanzapine treatment alters level of agitation at hospital discharge: Difference between olanzapine and placebo groups’ mean ABS score at discharge, controlling for ABS score at treatment commencement.To determine whether olanzapine treatment alters level of cognition in PTA: Difference between olanzapine and placebo groups’ mean levels of PTA as measured using the WPTAS [44, 45], controlling for WPTAS score at baseline. Mean scores will encompass daily assessments of the WPTAS throughout the treatment period, from first day of treatment until emergence from PTA (defined as the first of three consecutive days on which a score of 12 on the WPTAS is obtained). The WPTAS is commonly used in Australia to assess PTA. Seven items on the WPTAS assess orientation to time, person and place, and five assess anterograde memory (therapist face, name and three picture cards). Good construct validity and inter-rater reliability have been demonstrated [45, 61]. Nurses and clinical neuropsychologists who administer the WPTAS at Epworth HealthCare are trained in its use.To determine whether olanzapine treatment alters PTA duration: Difference between olanzapine and placebo groups’ mean number of days in PTA (from date of injury until emergence from PTA based on three consecutive scores of 12 on the WPTAS).To determine whether olanzapine treatment alters cognitive performance following PTA emergence:

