Difference between olanzapine and placebo groups’ mean total words recalled over five trials on the RAVLT [50]. The RAVLT is a 15-word cognitive list learning task. This test is sensitive to memory impairments in TBI populations [62] and has good psychometric properties [63].Difference between olanzapine and placebo groups’ mean number of items completed on the SDMT [51]. The SDMT is a test of processing speed, requiring transcription of numbers corresponding with symbols from a key over 90 s. Use of the oral version of this test will avoid effects of motor weakness on performance. The oral SDMT has excellent psychometric properties [64].Difference between olanzapine and placebo groups’ mean number of errors on the SDMT.

Epworth HealthCare clinical neuropsychologists who will administer these measures are trained and experienced in their use.
7.To determine whether olanzapine treatment alters length of inpatient hospital stay: Difference between olanzapine and placebo groups’ mean length of inpatient hospital stay, measured in days from day of admission until day of discharge from inpatient care.8.To determine whether olanzapine treatment alters functional independence at discharge and 3-month follow-up:

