### Sample size

Simulation studies by Teare et al. [71] indicate that small studies (less than 50 participants, 25 per group) do not provide realistic estimates of results, indicating that group sizes should be at least 25, and that preferably a minimum of 35 participants per group be employed where possible.

Although it did not specifically include the ABS, a recent systematic review [41] reported standardised mean differences (i.e. Cohen’s *d* or the difference in group means divided by the pooled group standard deviation) in 2-h and 24-h post-administration levels of agitation between intramuscular olanzapine and placebo ranging from 0.36 to 1.93. In regard to other populations, a study of agitation levels in patients with schizophrenia following administration of intramuscular olanzapine or placebo found a standardised mean difference of 1.27. The minimal clinically important difference for improvement in irritable/aggression scale scores in TBI [68] is equal to a standardised mean difference of 0.50, the conventional Cohen medium effect size, with a large Cohen effect size being defined as a standardised mean difference of 0.80. Given the above prior findings, a large effect size would be expected. Using the Stata 15 power and sample-size procedure, we calculated the required sample size to detect a standardised mean difference/effect size of 0.80 (e.g. 0.80 of the standard deviation of 4.1 for mean daily ABS score at outcome reported in the pilot study of McKay et al. [26], *n* = 125) with a statistical power of 0.80 and a 2-tailed alpha of 0.05. Results indicated a required sample size of 26 patients per group, for a total of 52 patients.

A sample size of 26 patients per group, or 52 in total, exceeds the lower threshold of 50 patients identified by Teare et al. [71] and is clinically practical. Assuming 10% attrition, 29 patients (26/(1–0.10) = 28.9, conservatively rounded to 29) per group would be required, for a total of 58 patients, in order to complete the study with 52 patients.

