### Statistical methods

#### Analysis of primary and secondary endpoints

Descriptive statistics will be reported using frequencies and percentages for categorical data. Percentages will be calculated based upon the number of patients for whom data are available. Continuous or dimensional variables will be summarised using means and standard deviations, with medians and interquartile ranges (difference between 25th and 75th percentiles) reported for potentially skewed data such as SF-12 PCS and MCS scores.

For the analysis of the primary endpoint, difference in mean daily ABS scores during PTA between olanzapine and control groups, a mixed model/multilevel regression framework [72], taking into account duration of PTA, will be employed. Although a difference between group means corresponding to a large effect size (0.80 of the pooled group standard deviation) is expected, a clinically significant improvement is defined as a difference in group means of the mean daily ABS scores within PTA equal to at least half a pooled group standard deviation difference, the minimal clinically important difference for improvement in irritable/aggression scale scores in TBI [68]. In regard to secondary endpoints, regression methods appropriate to the type of outcome variable will be employed. Comparison of the two groups on dimensional secondary endpoints such as ABS at discharge and WPTAS scores will be analysed using linear regression or median quantile regression. Median quantile regression, based upon the median and so less affected by very high or very low scores, will be employed for possibly skewed variables, such as SF-12v2 MCS and PCS scores, that may not meet the assumptions of linear regression [73].

Secondary endpoints involving count data including number of days in PTA, number of clinically agitated days, length of stay in hospital, agitation scores on discharge, number of “treatment failures” and number of AEs and other measures of treatment safety will be analysed using regression models for count data (Poisson or negative binomial regression as appropriate; [74]).

All statistical tests will be two-tailed, with alpha or statistical significance level set to *p* < 0.05. 95% confidence intervals will be reported throughout. The number of missing observations will be reported. Analyses will assume intention to treat, with all patients analysed as randomised.

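### PTA duration and length of stay include pre-randomisation days with no stated adjustment for them, which attenuates the estimated ratio and usually costs power

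*Protocol article*

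**What the plan says.** The Protocol article, Secondary outcomes, compares the groups on mean number of days in PTA, counted "from date of injury until emergence from PTA based on three consecutive scores of 12 on the WPTAS", and on mean length of inpatient stay, "measured in days from day of admission until day of discharge from inpatient care". Analysis of primary and secondary endpoints then groups these outcomes under "Secondary endpoints involving count data including number of days in PTA" and assigns Poisson or negative binomial regression as appropriate. No covariate is named for either outcome.

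Two neighbouring outcomes in the same list are handled differently. ABS at discharge controls for ABS at treatment commencement. Mean WPTAS controls for its baseline value and is averaged from the first day of treatment.

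Recruitment allows entry whenever agitation appears during PTA. Consent from the decision maker, eligibility screening and, for some, weaning from existing medication also have to be dealt with around entry. Randomisation therefore falls after injury and after admission, by an interval that varies between patients and is not reported.

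**The concern.** Olanzapine cannot change days that passed before randomisation. Including them in the outcome does two things. On the ratio scale used by a log-link count model, it adds the same expected quantity to both arms and moves the ratio towards 1. On any scale, it adds between-patient variation unrelated to treatment.

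Whether olanzapine alters PTA duration and length of stay are stated secondary aims. The Background raises prolonged PTA as a possible harm of antipsychotics, and the abstract says the trial will inform that question. With 58 participants, avoidable noise makes a null result less informative, and an attenuated ratio is easily misread as the effect on the time during which patients were treated.

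**Working it through.** **The plan's own figure.** The Sample size section sets out to "detect a standardised mean difference/effect size of 0.80" "with a statistical power of 0.80 and a 2-tailed alpha of 0.05", citing a "standard deviation of 4.1 for mean daily ABS score at outcome". The normal approximation gives 2 × (1.960 + 0.842)² / 0.80² = 24.5, so 25 per arm. With the noncentral t distribution, power is 0.791 at 25 and 0.807 at 26 per arm, which reproduces the "required sample size of 26 patients per group, for a total of 52 patients". Attrition of 10% gives 26 / 0.90 = 28.9, so 29 per arm. This concerns the ABS only. No variance, target effect or power is given for PTA duration or length of stay, so the durations below are assumptions.

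**Attenuation of the ratio.** Let P be the mean days before randomisation, Q the control mean afterwards and r the true ratio for the days afterwards. Counted from injury, the ratio is (P + rQ) / (P + Q). With Q = 20 and r = 1.5:

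- P = 10: (10 + 30) / 30 = 1.33
- P = 20: (20 + 30) / 40 = 1.25
- P = 30: (30 + 30) / 50 = 1.20

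The difference in means is 10 days in every case.

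**Added noise.** Take P = 20 with coefficient of variation (CV) 0.6 (SD 12), Q = 20 with CV 0.7 (SD 14; 21 in the prolonged arm), no correlation, 26 per arm.

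- Standard error of the difference from randomisation: √[(14² + 21²) / 26] = 4.95 days
- From injury: √[(14² + 21² + 2 × 12²) / 26] = 5.96 days
- Lead-in alone: 12 × √(2/26) = 3.3 days, so a chance gap of 1.96 × 3.3 ≈ 6.5 days lies at the edge of the 95% range, against a true effect of 10 days

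**Power for PTA duration.** Simulation with 26 per arm, gamma-distributed days, post-randomisation CV 0.7, negative binomial regression, 300 trials per row (Monte Carlo error about 3 points). The last column keeps the injury origin and adds log pre-randomisation days as a covariate.

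| Lead-in mean (CV) | Control days after | True ratio | Correlation | From injury | From randomisation | From injury, adjusted |
|---|---|---|---|---|---|---|
| 5 (0.6) | 30 | 1.75 | 0 | 0.86 | 0.85 | 0.86 |
| 20 (0.3) | 20 | 1.5 | 0 | 0.61 | 0.61 | 0.64 |
| 10 (0.6) | 20 | 1.5 | 0 | 0.58 | 0.62 | 0.64 |
| 20 (0.6) | 20 | 1.5 | 0 | 0.43 | 0.57 | 0.57 |
| 30 (0.6) | 20 | 1.5 | 0 | 0.33 | 0.58 | 0.58 |
| 20 (0.9) | 20 | 1.5 | 0 | 0.31 | 0.57 | 0.55 |
| 20 (0.6) | 20 | 1.5 | 0.5 | 0.34 | 0.58 | 0.73 |
| 20 (0.6) | 20 | 2.0 | 0 | 0.86 | 0.95 | 0.94 |
| 30 (0.6) | 20 | 2.0 | 0 | 0.77 | 0.95 | 0.95 |
| 30 (0.9) | 15 | 1.75 | 0.3 | 0.25 | 0.82 | 0.80 |

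Power from injury as a share of power from randomisation runs from about 1.0 (first two rows) to 0.25 / 0.82 = 0.30 (last row), a loss of up to about 70%.

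**Second distribution.** Lognormal durations (log-SD 0.5 before and 0.6 after, correlation 0.4, median 20 days after), 29 per arm, true ratio 1.5. Power from injury against from randomisation is 0.63 and 0.67 for a median lead-in of 5 days, 0.54 and 0.68 for 10, 0.38 and 0.70 for 25, and 0.24 and 0.66 for 40. Adjusting the injury-origin outcome for log lead-in days gives 0.74 to 0.77 throughout.

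**The case against.** The strongest reply is that the loss comes from a missing covariate, not from the outcome definition. Injury to emergence is a legitimate measure of PTA, adjustment recovers the power, and the article promises a detailed analysis plan that may name covariates. Most of this stands, and it is why keeping the stated origins is an acceptable fix. It does not dispose of the point. The article fixes origin and model here, names baseline covariates for two neighbouring outcomes, and names none for these. Adjustment also removes the noise but leaves the ratio describing total days since injury.

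A reader might also infer more than the document supports:

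- **That the analysis is biased towards no effect.** The stated outcome is a difference in mean days. Randomisation balances lead-in days in expectation, so a 10-day prolongation is still estimated as 10 days. The ratio correctly describes total duration. It is smaller than the ratio for days after randomisation.
- **That power is roughly halved.** Some assumed inputs give this and others give no loss. The document supplies none of the inputs.
- **That the PTA figures apply to length of stay.** They do not. Its lead-in is a different interval, and it was not simulated.
- **That count regression causes the dilution.** The time origin does. Overdispersion is a separate matter, and the plan permits negative binomial regression.
- **That the six-month limit censors PTA duration.** Treatment runs "until the patient is deemed to have emerged from PTA or until 6 months have elapsed", but the Post-PTA section has the remaining measures done on later emergence. Consent (General aspects) and Retention both provide for continued data collection after withdrawal. Some PTA end dates may still go unobserved, for example where that permission is refused, but no rate is given, so a switch to Cox or restricted-mean methods is a preference.

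**Conclusion.** The point holds as a matter of precision and interpretation, not of bias. Both outcomes contain pre-randomisation days, no adjustment for them is stated, the ratio is attenuated by simple arithmetic, and power is usually lower. In no simulated setting did the injury origin gain power beyond Monte Carlo error.

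The size cannot be fixed from the document. For PTA duration the loss runs from almost none, with a short or uniform lead-in, to about 70%, with a long and highly variable one. This rests on assumed lead-in means of 5 to 30 days, control means of 15 to 30 days after randomisation and true ratios of 1.5 to 2.0. For length of stay only the direction can be stated. Even the better analysis has only about 0.6 to 0.7 power for a ratio of 1.5 without adjustment, so a null result would be weak reassurance under either origin.

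**What to change.** For the treatment comparison, do one of the following:

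1. count days from randomisation to PTA emergence and from randomisation to discharge; or
2. keep the stated origins and pre-specify adjustment for log days from injury to randomisation (PTA duration) and from admission to randomisation (length of stay).

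The two give nearly the same power once lead-in days are a covariate. Where lead-in and later duration are correlated, including that covariate under option 1 helps as well: with correlation 0.5, power rose from 0.58 to 0.71. State which period the reported ratio refers to, and give the difference in mean days beside it. Total PTA from injury can still be reported.

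A time-to-event sensitivity analysis for participants whose PTA end is not observed is optional.

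The cost is wording in the outcome definitions and the analysis plan. Injury date, admission and discharge dates, randomisation date and daily WPTAS are already collected or on record, so no new data are needed.

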### Blinding

The on-site compounding pharmacy, the independent Epworth HealthCare accredited biostatistician who is responsible for creation of the randomisation schedule and the DSMC will be unblinded to group allocation. Olanzapine and placebo capsules will be as visually identical as possible to facilitate comparability of blinded interventions. Participants, MTDMs, ward staff, study staff and all investigators involved in the study will be blinded to treatment allocation. Unblinding will occur following data collection, once data cleaning has been completed.

Emergency unblinding may occur in response to an AE, where knowledge of treatment is required in order to manage the participant’s condition. This will occur in partnership with the DSMC, who will monitor outcomes and be informed of serious AEs and withdrawals. Any intentional or unintentional breaking of the blind will be reported and explained.

### Retention

To maximise data collection at 3 months post-discharge, participants and MTDM will be reminded at discharge that they will be contacted in 3 months, and told the approximate date of this contact. If a participant or MTDM fails to respond to attempts at 3-month contact, study staff will make every effort to regain contact (via telephone, email and, if necessary, a letter to their last known mailing address). These contact attempts will be documented. Should the participant continue to be unreachable, he or she will be considered to be lost to follow-up. These participants will not be withdrawn from the study, and existing data will be analysed.

Those participants who are withdrawn from the study before the cessation of PTA will be debriefed upon PTA emergence, and informed consent for the use of previously collected data and continuing data collection on outcome measures will be sought in order to allow for intention-to-treat analysis. There will also be continued recording of symptoms as per AE follow-up, if applicable. Any incidents of non-retention and reason for this will be documented.

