### Recruitment

Patients admitted to the Epworth HealthCare ABI Unit are routinely screened for PTA status using the WPTAS on admission. Those deemed to be in PTA have the WPTAS and ABS completed on a daily basis by a clinical neuropsychologist or nurse until they emerge from PTA. Study staff will be alerted to potential participants by ABI ward staff. Potential participants include patients in PTA who are exhibiting clinically significant agitation or thought likely to become agitated (due to factors such as agitation during acute hospitalisation). Due to their confusion and inability to lay down new memories, patients in PTA are not cognitively capable of consent. Recruitment will therefore target the patient’s MTDM. This will follow a two-stage process. Firstly, the study will be introduced to the patient’s MTDM by a member of their treating medical team and verbal consent for contact from study staff will be gained. Rapid consent processes are important to recruitment given the time-limited nature of PTA. The decision to introduce the trial to MTDMs of those patients determined likely to become agitated (rather than only those presently agitated) has been made in an effort to expedite the recruitment process and avoid exclusion of eligible participants. Agitation levels of those patients not presently agitated are monitored by study staff. If consent for contact is obtained and the patient is agitated at any stage during PTA, study staff will then contact the MTDM to carry out study consent procedures.

Participant recruitment commenced in June 2019, with the aim of recruiting participants until June 2022. Given that the full study protocol will have a duration of approximately 3 months, on average, data collection will continue until the end of September 2022. Epworth HealthCare treats more than 110 new patients with TBI annually, of whom 80 are likely to be in PTA on admission. Recent research studying this population within the Epworth HealthCare ABI ward [26] showed that 42.4% of TBI patients exhibited significant agitation according to the ABS whilst in PTA. Therefore, approximately 34 patients in PTA are likely to exhibit clinically significant agitation annually. Allowing for declined consent and ineligibility, we envisage recruitment of our sample over a 41-month period.

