#### Participant consent

Participant consent will be sought by study staff following that participant’s emergence from PTA and having been declared cognitively capable of consent by their treating clinical neuropsychologist. Failure to meet either of these criteria will result in the consent of the MTDM being maintained. In such cases, study staff will continue to monitor whether participants meet criteria for consent for the duration of their admission to the Epworth HealthCare ABI ward.

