Upon emerging from PTA as judged by a score of 12/12 on the WPTAS on three consecutive days, olanzapine will be tapered at a rate deemed appropriate by study doctors. Dose reduction or rechallenge may be undertaken in the setting of an adverse event (AE). Intervention may also be discontinued in the following circumstances: (1) following 6 months in PTA, (2) withdrawal of MTDM consent, (3) due to medical considerations or (4) escalation of agitation to an unmanageable level, resulting in physical aggression posing threat of harm to staff or property.

To maximise compliance, study staff will regularly check that treatment has been administered as prescribed by reviewing the participant’s medical chart. Study staff will also complete a treatment log, recording whether dosages have been administered, and dosage amount.

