### Rescue medication

In the event that agitation levels escalate to an unmanageable level such that this results in physical aggression posing threat of harm to staff or property, participants may be administered a rescue dose of olanzapine. This decision has been made in the interest of participant retention and to represent such highly agitated patients in the participant pool. Multiple incidents of rescue medication use will prompt consideration of withdrawal from participation by the trial Data Safety Monitoring Committee (DSMC) in consultation with the patient’s treating doctor and study psychiatrist.

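### Stopping study product is not consistently separated from leaving the study, and ABS data of patients withdrawn during PTA depend on consent sought at emergence, so data can be lost in a way related to the outcome

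*Protocol article*

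**What the plan says.** All references are to the protocol article.

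- **Intervention, randomisation and allocation** lists, among the circumstances in which the intervention may be discontinued, "escalation of agitation to an unmanageable level, resulting in physical aggression posing threat of harm to staff or property".
- **Rescue medication** allows rescue olanzapine for the same event, then adds: "Multiple incidents of rescue medication use will prompt consideration of withdrawal from participation by the trial Data Safety Monitoring Committee (DSMC"). The treating doctor and study psychiatrist are consulted.
- **Harms** has the DSMC advise on withdrawing participants for that event. Harms and the treatment-period text under Participant timeline both speak of withdrawal from the study as a possible response to serious adverse events.
- **Retention** says that patients withdrawn before PTA ends "will be debriefed upon PTA emergence, and informed consent for the use of previously collected data and continuing data collection on outcome measures" is then requested, with intention-to-treat analysis as the stated purpose.
- **Consent, General aspects** covers withdrawal of consent. Permission is then sought from the participant or MTDM for past data and for continued collection of measures the hospital takes anyway. No wait for emergence is stated.
- **Participant consent** says, of patients who have not emerged or are not yet capable: "Failure to meet either of these criteria will result in the consent of the MTDM being maintained".
- **Recruitment** says that ward patients in PTA "have the WPTAS and ABS completed on a daily basis by a clinical neuropsychologist or nurse until they emerge from PTA".
- **Primary outcome** uses every daily ABS in the treatment period, which ends at PTA emergence or at 6 months.
- **Analysis of primary and secondary endpoints** states: "Analyses will assume intention to treat, with all patients analysed as randomised".

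**The concern.** A decision by a clinician or the DSMC to take a patient off study product is not a withdrawal of consent. Apart from patients still in PTA at 6 months, the article does not say that such a patient stays in the study with daily ABS collected for analysis. If the decision is called withdrawal, the Retention rule applies. Even scores already collected under valid MTDM consent then depend on a later yes from the patient.

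Two features make this more than loose wording. First, the trigger is severe agitation, the construct that the primary outcome measures, so any loss is informative. Second, consent to further collection given at emergence cannot prospectively cover a window that ends at emergence; it can only release scores already on the ward chart.

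At stake are the primary contrast and the count of clinically agitated days. A patient whose series is cut on day 3 because of aggression can add at most about three agitated days, and so looks better than a similar patient who stays. The 10% attrition allowance in the sample size restores numbers but does not correct selective loss.

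**Working it through.** **1. The sections side by side**

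| Situation | Stated consequence | Stated handling of data |
|---|---|---|
| Still in PTA at 6 months | Product ceased | Later measures still taken |
| MTDM or participant withdraws consent | Withdrawal | Permission for past and routine data, from participant or MTDM, no wait stated |
| Not reached at 3 months | Not withdrawn | Existing data analysed |
| Unmanageable agitation | Product may be discontinued; or rescue, then withdrawal considered; or withdrawal on DSMC advice | If withdrawn during PTA: consent sought at emergence, for past data as well |
| Serious adverse event | Withdrawal from the study considered | As above |

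The first three rows show that the protocol can keep data after treatment or contact ends. The last two rows, where exit is related to agitation or tolerability, lack that protection.

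**2. The plan's own sample size**

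Inputs from the Sample size section: "we calculated the required sample size to detect a standardised mean difference/effect size of 0.80", "a statistical power of 0.80 and a 2-tailed alpha of 0.05", SD 4.1, 10% attrition. A two-sample t calculation gives 25.52, so 26 per group. Then 26/(1 − 0.10) = 28.9, so 29 per group and 58 in total. This reproduces the plan. The effect in points is 0.80 × 4.1 = 3.28. Power at this effect is 80.8% with 26 per group and 84.9% with 29.

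**3. Illustration of selective loss**

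The documents give no withdrawal rate, so the rates here are assumptions. Patient mean ABS is taken as normal with SD 4.1. One agitation level triggers withdrawal in both arms, and everyone above it contributes no ABS at all. With z the cut-off in SD units from the arm mean, the mean of those remaining lies φ(z)/Φ(z) SD below the full arm mean.

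*10% of placebo above the cut-off*
- Placebo: z = 1.2816, shift 0.1755/0.9000 = 0.1950.
- Olanzapine: z = 1.2816 + 0.80 = 2.0816, so 1.9% are above; shift 0.0457/0.9813 = 0.0466.
- Difference: 0.80 − 0.1950 + 0.0466 = 0.652 SD; × 4.1 = **2.67 points** (19% lower).

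*20% of placebo above the cut-off*
- Placebo: z = 0.8416, shift 0.2800/0.8000 = 0.3500.
- Olanzapine: z = 1.6416, so 5.0% are above; shift 0.1037/0.9497 = 0.1092.
- Difference: 0.80 − 0.3500 + 0.1092 = 0.559 SD; × 4.1 = **2.29 points** (30% lower).

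In simulation with 29 randomised per group, power is about 75% and 64%. The plan's threshold for clinical significance is 0.50 SD, or 0.50 × 4.1 = 2.05 points.

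**4. Sensitivity**

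- Half of the patients above the cut-off lost: 3.00 and 2.86 points.
- The same share lost from the top of each arm: the shifts cancel and the difference stays at 3.28.
- Scores before withdrawal kept: the bias is smaller. The documents do not allow this to be quantified.

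**The case against.** The case against is substantial, and much of it stands.

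- *Consent is not sought only at emergence.* A reader might infer that no permission can be had sooner. General aspects lets the MTDM give it, with no wait stated. That stands, but the route is written for withdrawn consent and is not linked to Retention.
- *Stopping product and leaving are not always merged.* A reader might infer that they are. The 6-month rule separates them, and Retention has an intention-to-treat purpose. That stands; the gap concerns agitation and adverse events.
- *The consequences are options.* A reader might infer that one event has three fixed outcomes. The wording is permissive throughout and can be read as graded, and rescue exists partly to retain highly agitated patients. That stands. What is missing is what each option means for data.
- *A closed window does not destroy data.* Ward ABS is recorded daily to emergence, so later permission can recover it. That stands; loss needs refusal, incapacity or lost contact. MTDM consent is kept in general for patients who lack capacity, but Retention does not say that this covers someone withdrawn by a clinician or the DSMC.
- *The analysis can cope.* A mixed model uses partial series, and imputation with sensitivity analysis is planned. This helps only with scores that the trial may use. Consent and retention rules decide that, not the SAP.
- *Loss mainly on placebo is assumed.* That stands: the article itself allows that olanzapine might increase or prolong agitation.

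**Conclusion.** The concern holds as an unreconciled set of rules that permits outcome-related loss of primary data. For patients withdrawn during PTA by a clinician or the DSMC, the Retention text makes even collected scores depend on a later consent. Following it could leave the most agitated patients out of an analysis that promises to include all as randomised.

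The documents do not show that this loss will occur, or how large it would be. The fall from 3.28 to 2.67 or 2.29 points is an upper-end illustration. It assumes 10% or 20% of placebo patients above a fixed agitation level common to both arms, and total loss of their ABS. A reader might take 19% to 30% as the expected bias; the documents support no such estimate. The bias needs unequal loss. In the scenario shown, which an effective drug would produce, it runs towards no effect.

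This should be fixed, but it does not invalidate the design. The stated sample size reproduces and is unaffected.

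**What to change.** Reconcile Consent (General aspects), Intervention, Rescue medication, the treatment-period text, Retention and Harms, so that stopping study product is distinct from leaving data collection. In Retention, state that unless the MTDM or participant expressly withdraws consent to data use:

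1. data already collected under MTDM consent are retained; and
2. the ward's routine daily ABS and WPTAS are abstracted to PTA emergence, and the ABS scores enter the primary outcome and the agitated-days count.

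Which clinical consequence follows unmanageable agitation or an adverse event is for the sponsor to decide; the sections only need to agree.

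The cost is protocol wording, an ethics notification or amendment, and some chart abstraction of scores that the ward already records. Trial status gives recruitment as 5, so at that point few patients would have fallen under the present text.
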